### Safety evaluation

Relevant safety indicators are recorded on the Subject Adverse Event Record Form by the acupuncturist at any time during treatment and follow-up:

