### Randomization and allocation concealment

The envelope randomization method will be used for randomization. Upon meeting both the inclusion and exclusion criteria, subjects will be enrolled into the study. The randomization personnel or clinical researchers will randomize them based on the pre prepared patient grouping envelopes. The randomization protocol for this study will be generated by the Clinical Evaluation Center at the subject’s institution, and this person will be not involved in the statistical analysis of this project. The randomization scheme for this study and the individual parameters set in the process of generating that scheme are collectively referred to as the blind bottom, which is sealed and signed by the person generating the randomization scheme and kept by a dedicated subject matter manager not involved in this project. Participants in subgroups are not involved in the statistical analysis of data. The evaluation of the efficacy indicators will be collected and organized by a person who is unaware of the subgroups, with a triple separation of the researcher, the acupuncture operator, and the statistician.

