### Blinding

Because this project is a needling treatment, the needling operator must be in direct contact with the patient, to whom blindness cannot be applied. However, blinding is implemented for all other personnel involved in the study (including patients, those who recorded and entered the observational indicators, and the data statisticians), who will be unaware of the specific grouping of patients. To guarantee a more effective execution of the blind approach, each patient will be treated individually as much as possible, minimizing the need for patients to discuss with each other about the acupuncture treatment method, their feelings during the acupuncture, and the effects of the treatment.

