#### Safety evaluation related to EA

Broken needles, missed needles, needle fainting, unbearable acupuncture-induced pain (VAS ≥ 8 points), localized hematomas, infections, and abscesses; symptoms, mean degree, and mean duration of other post-acupuncture discomfort (encompassing pain, dizziness spells, anorexia, headache, and insomnia that occurred ≥1 h in duration after acupuncture).

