#### Pregabalin adverse reactions

Distorted or overlapping vision, sleepiness, stomach discomfort, exhaustion, neuropsychiatric disturbances, other.

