## Limitations

This study has limitations due to the inherent flaws in the blinded implementation of acupuncture clinical trials. Despite our efforts to minimize potential bias by keeping statisticians and assessors blinded, operator knowledge of grouping is indeed unavoidable due to the nature of electroacupuncture treatment. In addition, patients may disrupt the blinding due to differences in treatment modalities, which may introduce bias into the study results. To minimize the interference of blinding limitations on the trial results, we will evaluate the blinding of operators and patients at the end of the trial, including operator-knowledge of the grouping, patient-perceived differences in treatments, and other factors that bias the blinding, such as differences in communication between operators and patients in different groups. In the meantime, we have referred to the relevant literature on similar studies (59, 60), and if bias occurs, we will assess the possible impact of each source of bias on the study results to estimate the extent of potential placebo effects and other biases. It is hoped that future studies will have better ways to address these limitations, and we will continue to monitor this issue.

Additionally, patients are required to visit the clinic on a weekly basis for three acupuncture sessions, each treatment takes more than an hour, the cost of time is greatly increased, and it is not as convenient as taking medication at home. For patients who face difficulties in frequently visiting the clinic, patient-self electroacupuncture treatment can be considered under the supervision of trained medical professionals. This form of treatment offers advantages such as enhanced convenience and personalized adjustments, aiding patients in their long-term management and rehabilitation. However, it also poses challenges including operational risks, variations in efficacy, substantial training requirements, and regulatory difficulties (61, 62). In our future research, we will delve deeper into the potential benefits and challenges associated with patient-self electroacupuncture.

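### Safety is to be compared between electroacupuncture and pregabalin, but an unblinded acupuncturist records it on treatment-specific lists with unequal thresholds

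*Protocol article*

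**What the plan says.** **Objective.** The Conclusion names effectiveness and safety of EA against medication as objectives. The Discussion looks ahead to EA as an option with few side effects.

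**Recorder.** Under Safety evaluation, the indicators are "recorded on the Subject Adverse Event Record Form by the acupuncturist at any time during treatment and follow-up". That sentence introduces both the EA list and the pregabalin list.

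**Blinding.** Under Blinding, "the needling operator must be in direct contact with the patient, to whom blindness cannot be applied". The same section says that everyone else is blinded, including "those who recorded and entered the observational indicators, and the data statisticians". Limitations concedes that "operator knowledge of grouping is indeed unavoidable due to the nature of electroacupuncture treatment". Under Randomization and allocation concealment, a blinded collector is named for efficacy: "The evaluation of the efficacy indicators will be collected and organized by a person who is unaware of the subgroups".

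**EA list.** "Broken needles, missed needles, needle fainting, unbearable acupuncture-induced pain (VAS ≥ 8 points), localized hematomas, infections, and abscesses", followed by "symptoms, mean degree, and mean duration of other post-acupuncture discomfort". That discomfort covers pain, dizziness, anorexia, headache and insomnia, and carries a duration condition of at least 1 hour after acupuncture.

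**Pregabalin list.** "Distorted or overlapping vision, sleepiness, stomach discomfort, exhaustion, neuropsychiatric disturbances, other". No duration condition is given, and no degree or duration is asked for.

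**Schedule.** Table 1 has separate safety rows for EA and for medication, both ticked at weeks 2 and 4. Course of treatment gives 12 EA sessions. The Medication group section describes oral capsules for 4 weeks and mentions no contact with the acupuncturist. The Abstract promises that adverse reactions will be watched for through the whole trial.

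**The concern.** A between-arm safety comparison needs the same question, with the same threshold, put in the same way to both arms, preferably by someone who does not know the arm. Here the recorder delivers one of the two treatments and knows who receives it. The named symptoms differ by treatment, and so does the rule for when a symptom counts.

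At stake is any statement that EA is safer or better tolerated than pregabalin. Such a statement would partly compare two collection methods. An analysis plan cannot repair this later, because a symptom that was not prompted for, or that was screened out by a threshold in one arm, is not in the data. The primary pain outcome is not affected.

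**Working it through.** The document states no safety figure, so there is none to reproduce. The check sets the sections side by side.

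1. **Is the recorder blinded?** Safety evaluation names the acupuncturist. Blinding and Limitations both say the operator knows the grouping. The recorder is therefore unblinded. If the observational indicators in the Blinding section include safety, that section conflicts with Safety evaluation. If they do not, safety simply falls outside the blinding. Either way, blinded collection is specified for efficacy only.

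2. **Are the same symptoms named?** Leaving out needle-specific events:

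| Feature | EA list | Pregabalin list |
|---|---|---|
| General symptoms named | pain, dizziness, anorexia, headache, insomnia | vision change, sleepiness, stomach discomfort, exhaustion, neuropsychiatric disturbances |
| Duration condition | at least 1 h after acupuncture | none |
| Degree and duration recorded | yes | not stated |
| Open category | other discomfort, tied to acupuncture | other |

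No symptom term stands on both lists. Some entries may overlap in meaning: insomnia could be filed under neuropsychiatric disturbances, for example. That choice is left to the recorder.

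3. **Could each list serve both arms?** The EA duration condition runs from a needling session, and a drug-arm patient has none. As worded, that list cannot be applied to the drug arm. The section headings and the two separate rows in Table 1 point the same way. The text does not say outright that each list is confined to one arm, so this step is an inference.

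4. **Is contact with the recorder comparable?** EA arm: 3 sessions per week × 4 weeks = 12 sessions. Drug arm: no comparable contact is described. The formal safety rows in Table 1 are equal in number, at two visits each. The difference lies in the recording allowed at any time, which is easier when recorder and patient meet 12 times.

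5. **Which way would the bias run?** More contact would raise the EA count. The 1-hour condition, and recording by the person who gives the treatment, could lower it. The open category for pregabalin has no threshold, which could raise the drug-arm count. These pull in different directions, and the document gives no detection rates. Neither the sign nor the size of the net bias can be derived.

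**The case against.** The strongest reply is that the lists only name expected reactions. The pregabalin list ends with an open category, the EA list covers other discomfort after acupuncture, and the Abstract promises monitoring of adverse reactions in general. The article also condenses a fuller protocol. The record form and the operating procedures are not shown and may hold common prompts. Needle events can only occur with EA, so some treatment-specific listing is proper.

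Much of this stands, and it rules out several stronger readings:

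- A reader might infer that unlisted symptoms are never recorded in the other arm. The open category and the Abstract do not support that.
- A reader might infer that the acupuncturist never meets drug-arm patients. The article is silent on this, and naming the acupuncturist as recorder of pregabalin reactions implies some contact or relay.
- A reader might turn 12 sessions against 2 visits into a detection ratio. That needs independent events at each contact and no recall between visits, and nothing in the document supports either. Both Table 1 safety rows are ticked at the same two visits.
- A reader might see Table 1 as contradicting safety recording in follow-up. The separate adverse-events row shows a single tick, which may be a merged cell across all visits, so the table is not reliable evidence of a conflict.

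The reply does not reach the core. An open category is not the same as a named prompt, and a general promise equalises neither recorder nor threshold nor contact. The unblinded recorder, the two lists and the one-sided duration condition are stated in the article itself, not inferred from an omission.

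**Conclusion.** The point holds in this form: the protocol sets a comparative safety objective but collects safety through an unblinded treating operator, on treatment-specific lists, with a duration threshold on the EA side only. Ascertainment is therefore unequal as specified, and a between-arm difference in non-serious symptoms could not be attributed to treatment with confidence.

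No magnitude is claimed, because neither direction nor size is known. The conclusion rests on reading each list as belonging mainly to its own arm, which the headings, the Table 1 rows and the timing condition support. It also rests on the unseen record form not overriding the printed rules. The unblinded recorder and the unequal threshold do not depend on the first of these. The efficacy results are untouched. This is a cheap improvement, not a fault that undermines the trial.

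**What to change.** In the Safety evaluation section and its two lists:

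- Add one common checklist holding the general symptoms of both lists, with the same duration threshold for both arms or none, plus one open question.
- Have participants in both arms complete it themselves at the existing week 2, 4, 8 and 12 visits, after the efficacy scales. Keep it from the blinded efficacy assessor and the HAMD rater. If the blinded assessor asked the questions, the answers could reveal the arm and carry over to later visits.
- Base the main between-arm comparison of non-serious symptoms on this checklist.
- Continue to record spontaneous and serious events at any time in both arms, and report them by arm, so that events between visits are not lost.
- Report procedure-specific events (broken or missed needles, needle fainting, hematoma, needle-site infection or abscess, acupuncture-induced pain) descriptively for the EA arm only.
- State in the Blinding section whether safety indicators count among the blinded observational indicators.

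**Cost:** a revised form, a few minutes at each existing visit, and more minor symptoms recorded in both arms. Self-completion does not blind the participants, whose treatments visibly differ, so some reporting bias may remain. What it removes is the dependence on the treating operator, on different prompts and on unequal contact.

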#### Safety evaluation related to EA

Broken needles, missed needles, needle fainting, unbearable acupuncture-induced pain (VAS ≥ 8 points), localized hematomas, infections, and abscesses; symptoms, mean degree, and mean duration of other post-acupuncture discomfort (encompassing pain, dizziness spells, anorexia, headache, and insomnia that occurred ≥1 h in duration after acupuncture).

#### Pregabalin adverse reactions

Distorted or overlapping vision, sleepiness, stomach discomfort, exhaustion, neuropsychiatric disturbances, other.

### Quality control and data management

First of all, the research group will formulate the unified Standard Operating Procedures (SOPs), and prior to the official commencement of the clinical trial by 1 month, the research team will organize a dedicated training session aimed at imparting standardized training to all researchers participating in the study. The core emphasis of the training revolves around the project’s execution plan and the adherence to various SOPs. This is to ensure that every clinical researcher is thoroughly acquainted with the research methodology, including the intricate implementation details, thereby guaranteeing the credibility and authenticity of the clinical research findings.

Furthermore, all observations recorded during clinical studies must undergo rigorous verification and multiple rounds of confirmation to uphold the reliability and authenticity of the data. This approach ensures that every result and conclusion presented in clinical studies is derived solely from the primary, unadulterated data, maintaining the integrity of the research outcomes. Expert data administration companies are commissioned to conduct clinical data management, and monthly clinical research quality checks are strictly implemented. Reasons for withdrawal will be systematically recorded for all participants who discontinue the trial at any stage, and the resulting dropout rate will be statistically analyzed.

### Sample size estimation

This research involves a randomized controlled trial design, where eligible participants will be allocated to two distinct groups in an equal proportion of one participant to another (1:1 ratio), and the primary outcome metric is the percentage of cases with a pain intensity VAS ≤ 2 points after 4 weeks of treatment. According to the project team’s pre-efficacy observation pre-trial, the effective rate of this study’s treatment regimen in treating PHN is about 91%, and the literature reported that the effective rate of pregabalin is 74.4% (49). The estimation of the required sample size formula for the test of superiority of the independent sample rate of two groups is used for the calculation, taking *α* = 0.025 and *β* = 0.2, with the same number of sample cases between the groups, and using a one-sided test, taking into account a 20% dropout rate. Each group will necessitate a minimum of 62 cases, resulting in a combined total of 124 cases across the two groups.

$$N=\frac{2{\left[Z_{\alpha /2}\sqrt{2\bar{p}\bar{q}}+Z_{\beta }\sqrt{p_{0}q_{0}+p_{1}q_{1}}\right]}^{2}}{{\left(p0-p1\right)}^{2}}$$

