**Methods and analysis:**

The protocol outlines a double-center, randomized, and controlled trial design where both patients and assessors are blinded to the intervention being administered. The duration of the trial’s therapeutic intervention will span 4 weeks, followed by a 2-month observation period for monitoring any subsequent effects or outcomes. The 124 qualified individuals will be randomly allocated in a balanced 1:1 ratio to either the EA group or the drug group. All variables will undergo evaluation at the start of the study (week 0, baseline), during the treatment period at weeks 2 and 4, and during the follow-up period at weeks 8 and 12. The primary outcome is the Visual Analog Scale (VAS). Secondary outcomes include the Brief pain inventory-Facial scale (BPI-Facial), Pittsburgh Sleep Quality Index Scale (PSQI), Self-rating depression scale (SDS), Hamilton depression scale (HAMD), and Quality of Life Rating Scale (SF-36). The occurrence of any adverse reactions will be monitored and assessed throughout the duration of the trial.

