#### Inclusion criteria

Meets the diagnostic criteria in the 2016 Chinese Expert Agreement on Diagnosis & Treatment of PHN (41);History of herpes zoster of the head and face with healed and resolved head and face lesions, neuralgia symptoms persisting ≥1 month after lesion healing, baseline facial pain profile score ≥4, and abnormal sensation and pain sensitivity of the skin around the lesions;50 ≤ Age≤80 years, gender not limited;Consciousness, pain perception and discrimination, able to complete fundamental communication; andParticipants who have willingly given their informed consent to join this research.

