### Outcome measures

#### Primary outcome measure

The Visual Analog Scale (VAS) allows patients to self-assess the intensity of head and facial pain by marking a point on a graduated straight line, ranging from 0 (indicating no pain) to 10 (representing the worst intolerable pain), with higher scores indicating greater pain severity. To elaborate, a score of 0 signifies the absence of pain; scores ranging from 0 to 3 denote mild and manageable pain; scores between 4 and 6 indicate pain that interferes with sleep yet remains tolerable; while scores from 7 to 10 represent severe and intolerable pain that significantly disrupts sleep or other daily activities. It is the most widely utilized tool for evaluating subjective symptoms, particularly in measuring pain severity (42, 43).

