### Statistical analysis

The statistical analysis of the data will be independently conducted by a third-party statistician, unaffiliated with the pre-test phase, utilizing the SPSS 25.0 software. Measurements are described as mean ± standard deviation (
$\bar{x}\pm s$
), median, maximum, minimum, and quartiles, and counts are expressed as percentages (%). All hypothesis tests will be conducted using a two-tailed approach, with statistical significance being determined at a threshold of *p* < 0.05. Baseline data will be evaluated for between-group comparability with a two-tailed statistical test at the *α* = 5% level. For count data, the chi-squared test will be employed to analyze differences between groups. For measured data, the t-test will be utilized to compare groups. And for nonparametric variables, the Wilcoxon rank-sum test will be adopted to assess group comparisons. Baseline data will be compared between groups with two-tailed statistical tests at the α = 5% level. If the data conform to normal distribution and is chi-square, t-test for independent samples will be employed to compare differences between groups, whereas a paired t-test will be utilized to assess changes within the same group over time or under different conditions. The chi-square test will be used for count data, and nonparametric tests will be used for comparison of rank data and data not conforming to normal distribution. At a significance level of *α* = 0.05, a *p*-value less than 0.05 (*p* < 0.05) suggests that the observed difference is statistically significant. After all data entry and checking are completed, the statisticians will carry out the statistical analysis work in a timely manner and issue a written statistical analysis report.

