In addition, the VAS is selected as the primary outcome measure for evaluating EA efficacy in treating cephalo-facial PHN, primarily due to its ability to continuously and quantitatively capture dynamic changes in pain intensity. VAS provides high sensitivity in reflecting patients’ subjective pain experiences, with operational simplicity that facilitates the detection of both immediate and cumulative analgesic effects induced by EA. As an internationally validated pain assessment tool, VAS aligns closely with the neurophysiological mechanism of EA (modulating neural signal transmission), and its score changes directly validate the achievement of the primary therapeutic goal (pain relief). This offers a standardized basis for clinical decision-making and inter-study efficacy comparisons. The BPI-Facial is chosen as a secondary outcome measure to address the unique distribution (e.g., trigeminal nerve regions) and complex characteristics (e.g., burning sensation, allodynia) of cephalo-facial PHN. BPI-Facial enables multidimensional evaluation of EA’s comprehensive effects, including pain intensity, quality, and interference with emotions, sleep, and daily functioning. This complements the limitations of VAS by providing a broader perspective on treatment efficacy. Additionally, analyzing pain-related quality-of-life impairments helps verify the potential mechanisms through which EA improves overall health status. The PSQI is included as a secondary outcome to systematically assess the impact of pain on sleep architecture. Cephalo-facial PHN often causes severe sleep disturbances due to pain, and PSQI quantifies the indirect sleep-improving effects of EA via pain relief. It also elucidates the interrelationships between sleep recovery, pain reduction, and quality-of-life enhancement, offering indirect evidence for EA’s multi-target regulatory mechanisms. The SDS and HAMD are selected as secondary measures to rapidly screen for depressive symptoms induced by chronic pain. These tools quantify the indirect psychological benefits of EA through somatic symptom relief (e.g., pain) and reveal the bidirectional relationship between pain and depression. This is particularly relevant for cephalo-facial PHN patients, who are prone to comorbid moderate-to-severe depression due to prolonged pain. SDS and HAMD provide supplementary evidence for EA’s “holistic” (somatic-psychological) efficacy and strengthen the comprehensive assessment of health outcomes. The SF-36 is adopted as a secondary outcome to evaluate multidimensional health states, including physiological, psychological, and social functioning. It quantifies the overall quality-of-life improvements resulting from pain relief and systematically reflects EA’s comprehensive effects on daily activity capacity, emotional well-being, and social participation across its eight domains. This provides standardized evidence for the sequential efficacy of EA (“pain relief-functional recovery-quality-of-life enhancement”) and enhances the quantitative assessment of holistic health benefits.

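### The primary endpoint is the VAS score in some sections and the percentage with VAS ≤2 at week 4 in another, so the deciding test is not fixed

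*Protocol article*

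**What the plan says.** Four parts of the protocol article bear on the primary endpoint.

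- **Abstract, Methods and analysis:** "The primary outcome is the Visual Analog Scale (VAS"), with no summary measure, threshold or primary visit. On timing it says: "All variables will undergo evaluation at the start of the study (week 0, baseline), during the treatment period at weeks 2 and 4", and it goes on to weeks 8 and 12.
- **Primary outcome measure:** patients rate pain by "marking a point on a graduated straight line, ranging from 0 (indicating no pain) to 10 (representing the worst intolerable pain"). The section sorts scores into bands (0–3, 4–6, 7–10). It gives no cut at 2 and no primary visit.
- **Discussion:** the VAS was chosen "primarily due to its ability to continuously and quantitatively capture dynamic changes in pain intensity", and score changes are said to show whether the therapeutic goal is met.
- **Sample size estimation:** "the primary outcome metric is the percentage of cases with a pain intensity VAS ≤ 2 points after 4 weeks of treatment". The calculation is for two independent proportions, 91% against 74.4%.

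Statistical analysis then assigns tests by type of data: chi-squared for counts, "For measured data, the t-test will be utilized to compare groups", and rank tests for non-normal data. It names no test for the primary outcome and treats any p below 0.05 as significant.

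**The concern.** A score on a 0–10 scale and a proportion below a cut-point are different endpoints, with different estimates and different tests. One trial can succeed on one and fail on the other. Because the test follows from the data type, the conflict over the endpoint becomes a conflict over which p-value decides the trial. Nothing in the text prevents that choice from being made after the results are known.

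The sample size is affected too. It is calculated for the proportion only, so if the score is primary the protocol has no sample-size justification at all.

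**Working it through.** **1. The definitions side by side.**

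| Section | Variable | Summary | Primary visit | Test implied |
|---|---|---|---|---|
| Abstract | VAS | none given | none given | not stated |
| Primary outcome measure | VAS, 0–10 | none given | none given | not stated |
| Discussion | VAS as a continuous score | score changes | none given | t-test or rank test |
| Sample size estimation | VAS ≤2 | percentage | week 4 | chi-squared |

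Week 4 is the only primary time point stated anywhere, and it appears only in the last row.

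**2. The plan's own sample size.** Inputs from Sample size estimation: p1 = 0.91, p0 = 0.744, one-sided α = 0.025 (z = 1.96, the same critical value as two-sided 0.05), β = 0.2 (z = 0.8416), 20% dropout, 62 per group stated.

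- Mean proportion = (0.91 + 0.744)/2 = 0.827. √(2 × 0.827 × 0.173) = 0.5349.
- √(0.91 × 0.09 + 0.744 × 0.256) = 0.5219.
- n = (1.96 × 0.5349 + 0.8416 × 0.5219)² / 0.166² = 1.4876² / 0.02756 = 80.3, so 81 evaluable per group.
- With 20% dropout: 81/0.8 = 101.25, so 102 per group (204 in total).

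The stated 62 is not reproduced. Unpooled, arcsine and continuity-corrected forms at the stated α give 78, 77 and 92 before dropout, so they do not give it either.

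**3. Power for the responder endpoint.** Power = Φ[(0.166√n − 1.96 × 0.5349)/0.5219].

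- n = 62: (1.3071 − 1.0484)/0.5219 = 0.496, power 69%.
- n = 50 (62 × 0.8 = 49.6): (1.1738 − 1.0484)/0.5219 = 0.240, power 59.5%. At n = 49 it is 58.6%.

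**4. The score endpoint.** The article gives no mean difference or SD for the VAS, so no power can be stated. What can be given is the standardised difference detectable with 80% power at two-sided 0.05, (1.96 + 0.8416)/√(n/2): 0.50 SD with 62 per group and 0.56 SD with 50. By assumption, true differences of 0.4, 0.5, 0.6 and 0.7 SD need 99, 63, 44 and 33 evaluable per group, or 124, 79, 55 and 42 after 20% dropout.

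**5. Cost of leaving the test open.** Two tests at 5% each have a combined false-positive rate between 5% (always agreeing) and 10% (never rejecting together). The score test and the responder test at week 4 use the same data, so the rate lies between these limits. It was simulated under no effect: 20,000 trials, 50 per group, normally distributed scores, between-visit correlation 0.5 to 0.8.

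- Week-4 t-test or week-4 chi-squared test: about 8–9%.
- Those two plus t-tests at weeks 2, 8 and 12: about 14–19%.

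These rates are two-sided. About half of the rejections would favour electroacupuncture: roughly 4% for the week-4 pair, against a nominal 2.5%.

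**The case against.** The strongest reply is that this is a condensed article, and an analysis plan that is not shown may name the primary test. That would excuse silence, but it does not excuse contradiction. No analysis plan can adopt one definition without overruling either Sample size estimation or the Abstract and Discussion.

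A second reply is that a responder rate is a legitimate endpoint, and the only version for which the article gives a visit and planning values. This stands: either definition, used consistently, removes the contradiction. The planning values are themselves loose, however. The article says that "the effective rate of this study’s treatment regimen in treating PHN is about 91"%, and neither that rate nor the 74.4% is tied to VAS ≤2.

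A reader might also infer stronger points that the article does not support.

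- **That the trial is powered for the less informative version.** It is sized on that version, but step 3 shows that it does not reach 80% power for it. Sizing on a less efficient endpoint would not in itself underpower an analysis of the score.
- **That the score would have about 92% power.** This follows if both rates come from equal-variance normal scores 0.69 SD apart. The rates are not defined on the VAS, and the model fits the scale poorly: at an SD of 2 the electroacupuncture mean would be 2 − 1.34 × 2 = −0.68, below the bottom of the scale.
- **That five tests compete as primary.** The 14–19% figure requires this, but week 4 is the only primary visit stated.
- **That patients could enter already meeting VAS ≤2**, because eligibility uses a "baseline facial pain profile score ≥4". The name is unclear, no figure shows that this would happen, and it has no bearing on which endpoint is primary.

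**Conclusion.** The contradiction is real, lies within the article and must be resolved before any data are analysed. The supported consequence is that the choice between a score test and a chi-squared test at week 4 is open. Made after seeing the data, that choice raises the two-sided false-positive rate from 5% to about 8–9%. This rests on normal scores and 50 evaluable per group, and it describes what the text permits, not what the investigators intend. The higher range of 14–19% applies only if other visits were also treated as primary.

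The power of 69%, or about 59% after the planned dropout, applies to the responder endpoint and takes 91% and 74.4% as VAS ≤2 rates, which the article does not establish. For the score endpoint, power is unknown.

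**What to change.** State one variable, one summary measure, week 4 as the time point and one named test, used once at two-sided 0.05. Use the same words in the Abstract, Primary outcome measure, Sample size estimation, Statistical analysis and Discussion. Label the other version of the endpoint and the visits at weeks 2, 8 and 12 secondary.

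The week-4 VAS score, compared between arms with adjustment for baseline VAS, fits the Discussion's rationale and generally uses more of the data. VAS ≤2 at week 4 would then be a secondary responder analysis. If the sponsor prefers the responder rate as primary, the Abstract, Primary outcome measure and Discussion must say so.

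In either case, rewrite Sample size estimation for the chosen endpoint. The score needs a justified difference and SD. The responder rate needs planning rates defined as VAS ≤2 and a corrected number or an honest statement of power; the present inputs require 102 per group.

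The cost is consistent wording and one recalculated paragraph. If the score is chosen, the headline result is slightly less direct for clinicians than a responder rate, which remains available as secondary.
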